### Oral screen intervention

We will use the IQoro® oral screen device for this study. This device is designed to strengthen the facial muscles [21], the oropharyngeal muscles, and the esophageal muscles [22]. Moreover, it increases activity in all muscles, from the lips down to the diaphragm [22]. The training protocol specifies using the device actively for 30 s, three times a day, before meals. Briefly, the oral screen is placed in the mouth, predentally, behind closed lips. The participant is asked to close the lips around the oral screen, to maintain it inside the lips; then, the participant pulls the handle horizontally, straight forward, as if to pull it out of the mouth, for approximately 5–10 s. The pulling force should be as high as possible without losing grip of the handle (see Fig. 1). The pulling maneuver is performed three times, with a 3-s rest between each maneuver [21]. When a participant cannot manage training independently (e.g., unable to close the lips or unable to pull the handle), a staff member is instructed to assist, with information about possible modifications in the training.

**Fig. 1 Fig1:**
[figure not shown]
Oral screen training. (*Left*) The oral screen is inserted predentally, behind closed lips. (*Right*) The patient must press the lips firmly together, then strongly pull the handle straight forward, away from the mouth, and maintain pressure for 5–10 s. Illustrations: [name]©

The participants in the intervention group will be asked to treat the dysphagia displayed at baseline by undergoing oral screen training for 5 weeks. The clinical assessments and self-reported measures (described above) will be collected at baseline, immediately after the intervention, and at 6 months post-intervention (see Fig. 2).

**Fig. 2 Fig2:**
[figure not shown]
Flow-chart of the subject inclusion and data collection processes. ^a^ See Table 1

The control group will be asked to undergo the same assessments at the same times as the intervention group. Control participants will be given standard care (e.g., adjustments in food consistencies and posture instructions), according to the routines in the short-term care unit, where they reside. The data collection process is described chronologically in Fig. 2.

### Sample size calculation

In study 2, the primary outcome variables will be the changes in swallowing capacity (based on the SCT), measured at the start and end of treatment, and at follow-up, 6 months later. The sample size calculation will be based on the assumption that the data will be normally distributed. To retain an overall type I error of 5%, the type I error will be set to 2.5% for the primary endpoint. Based on historical data, we assume that the standard deviation of the change in SCT level will be 3 ml/s. To detect a critical difference of 2.8 ml/s in swallowing capacity between the intervention and control groups with a power of 80% and type I error of 2.5%, a sample size of at least 22 subjects would be required to fulfill the study protocol in each group. The total number of subjects included must be somewhat higher, to compensate for drop-outs.

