**Methods/Design:**

This project consists of two parts, which will be performed in five Swedish counties. It will include approximately 400 older individuals and 200 healthcare professionals. Part 1 is a cross-sectional, descriptive study of older people admitted to short-term care. Subjects will be assessed by trained professionals regarding oral health status, oral HRQoL, eating and nutritional risk, and swallowing ability. Swallowing ability will be measured with a teaspoon test and a swallowing capacity test (SCT). Furthermore, subjects and staff will complete a questionnaire regarding their perceptions of care quality.

Part 2 is a cluster randomized intervention trial with controls. Older participants with dysphagia (i.e., SCT <10 ml/s, measured in part 1) will be recruited consecutively to either the intervention or control group, depending on where they were admitted for short-term care. At baseline, all subjects will be assessed for oral health status, oral HRQoL, eating and nutritional risk, swallowing ability, and swallowing-related QoL. Then, the intervention group will receive 5 weeks of training with an oral screen for neuromuscular training focused on orofacial and pharyngeal muscles. After completing the intervention, and at six months post-intervention, all assessments will be repeated in both study groups.

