### Design and setting

The SOFIA project consists of two main parts; part 1 is a descriptive, cross-sectional study (aims *i* and *ii*), and part 2 is a cluster randomized, controlled trial (aim *iii*).

Data collection will take place in 32 short-term care units, located in five Swedish counties, in both rural and urban areas. The short-term care units are diverse in organization and staffing; they may be one section of a care home or an independent short-term care unit.

Participating short-term care units will be selected, based on informed consent from the heads of social welfare services and unit managers; the number of beds; the estimated number of discharges per month; and the geographic location. The sample in part 1 will comprise approximately 400 older participants. All participants will be assessed at baseline, and participants that exhibit low swallowing capacity (i.e., <10 ml/s) will be asked to participate in the interventional part of the study (part 2). In part 2, participating older persons will, after informed consent, be randomized into either the intervention or the control group, based on where they were admitted for short-term care. In addition to the baseline assessments, all participants in part 2 will be assessed after the intervention is completed (5 weeks) and 6-months post-intervention. The follow-up assessments will be conducted at the study participant’s location (e.g., in the short-term care unit, in the individual’s own home, or in a care home, where the older person resides at that time).

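### The 22 per group for 80% power is a sample size for independently randomised subjects; under the declared cluster design the stated 80% does not hold

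*Protocol article*

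**What the plan says.** The abstract states the design of the trial: "Part 2 is a cluster randomized intervention trial with controls". Under Design and setting, participants will "be randomized into either the intervention or the control group, based on where they were admitted for short-term care", so the care unit is the unit of allocation. Methodological considerations lists cluster randomisation among the design's strengths. The only count of units is for the project as a whole: "Data collection will take place in 32 short-term care units, located in five Swedish counties". How many of them feed part 2, and how they divide between arms, is not given.

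The Sample size calculation section takes the change in swallowing capacity (SCT) as primary outcome. It assumes normal data and an SD of change of 3 ml/s, and seeks a difference of 2.8 ml/s "with a power of 80% and type I error of 2.5"%. On the error rate it says: "To retain an overall type I error of 5%, the type I error will be set to 2.5% for the primary endpoint". The result is that "a sample size of at least 22 subjects would be required to fulfill the study protocol in each group". The only stated reason to recruit more is attrition, for which no rate is given. Statistical methods names independent-sample t-tests for comparing intervention with control on continuous variables.

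**The concern.** When whole units are allocated, participants in one unit tend to resemble each other, and the information in a fixed number of participants falls. The article itself gives grounds to expect this. Its Background names differing skill mixes and staffing levels between care units as confounders in this setting, and the control group receives standard care according to each unit's own routines. A sample size derived as if individuals had been randomised therefore belongs to a different design from the one declared.

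At stake is the meaning of the stated 80%. Anyone who relies on it when reading a non-significant result would credit the trial with more ability to detect 2.8 ml/s than it has.

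**Working it through.** **Inputs from the article (Sample size calculation):** difference d = 2.8 ml/s; SD of change s = 3 ml/s; type I error 2.5%; power 80%; 22 completers per group. Sidedness is not stated.

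**1. Reproduce the stated figure.** For two independent means under the normal approximation, n per group = 2 (z for alpha + z for power)² (s/d)².

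- Two-sided 2.5%: 2 × (2.2414 + 0.8416)² × (3/2.8)² = 21.82, rounded up to 22. Power at 22 is 80.3%. This reproduces the article.
- One-sided 2.5%: the same formula gives 19 after rounding up. This does not reproduce it.

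So 22 is the two-sided result for independent subjects, with a design effect of 1.

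**2. Is a clustering allowance hidden in it?** The only slack is the rounding: 22 / 21.82 = 1.008. If 44 completers were spread evenly over all 32 units (44/32 = 1.375 per unit), a design effect of 1.008 corresponds to an ICC of 0.008 / 0.375, about 0.02. Nothing beyond that is covered.

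**3. The named test, still without clustering.** The standard error is 3 × √(2/22) = 0.9045, so the noncentrality is 2.8 / 0.9045 = 3.096. With 42 degrees of freedom the two-sided 2.5% critical value is 2.325. The noncentral t distribution gives 77.7% power at 22 per group, 79.7% at 23 and 81.7% at 24. So 24 per group would be needed before any correlation enters.

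**4. With clustering.** The ICC and the units per arm (k) are not in the article, so both are assumed here. Take m = 22/k participants per unit, equal unit sizes, design effect DE = 1 + (m − 1) × ICC, standard error √(2 × 9 × DE / 22), and a t reference with 2k − 2 degrees of freedom. The unit-level degrees of freedom presuppose an analysis that respects the allocation; the article names only the ordinary t-test.

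| Units per arm (assumed) | m | df | ICC 0 | ICC 0.05 | ICC 0.10 | ICC 0.20 |
|---|---|---|---|---|---|---|
| 16 | 1.375 | 30 | 76.5% | 75.7% | 74.8% | 73.2% |
| 8 | 2.75 | 14 | 71.6% | 67.6% | 63.9% | 57.2% |
| 6 | 3.67 | 10 | 67.7% | 61.7% | 56.4% | 47.8% |

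**5. Separate the sources of loss.** The ICC 0 column holds the loss from degrees of freedom alone; moving right along a row adds the loss from correlation.

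- 16 units per arm, ICC 0.10: from 80.3% to 77.7% by using t instead of z (2.6 points), to 76.5% by using unit-level degrees of freedom (1.2 points), to 74.8% by correlation (1.7 points).
- 16 units per arm, ICC 0.05 to 0.20: correlation alone costs 76.5 − 75.7 = 0.8 to 76.5 − 73.2 = 3.3 points.
- 8 units per arm, same ICC range: 71.6 − 67.6 = 4.0 to 71.6 − 57.2 = 14.4 points.
- 6 units per arm, same ICC range: 67.7 − 61.7 = 6.0 to 67.7 − 47.8 = 19.9 points.

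**The case against.** **Clustering may cost very little here.** The only unit count in the article is 32. If every unit contributes evenly there are about 1.4 completers per unit, and the design effect is 1.02, 1.04 and 1.075 at ICC 0.05, 0.10 and 0.20. On the article's own normal approximation, power is then 79.5%, 78.7% and 77.2%, and 23 to 24 per group would restore 80%. This stands, and it limits the size of the point. It does not remove it: the 32 units serve the whole project, recruitment is consecutive, and the units are described as diverse in organisation, so an even spread is not assured.

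**The figure is a minimum.** The article says at least 22 and expects to include more, and part 2 draws on about 400 people assessed in part 1. A larger sample could restore the power. But the stated reason for exceeding 22 is drop-out, and 22 is the number meant to complete. This mitigates the point and does not answer it.

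**An article condenses.** A fuller document might treat clustering. However, this article prints the inputs and the result, and they reproduce with a design effect of 1. Further detail elsewhere cannot make 22 per group equal 80% under the named test.

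**A stronger reading.** A reader might infer that part 2 is badly underpowered, with power near one half. The documents do not support that. The low figures in the table need few contributing units and a high ICC, neither of which the article states, and much of the drop with few units comes from degrees of freedom and not from correlation. Nor do the documents support one particular larger sample size, since that depends on whether extra participants come from new units or from those already included.

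**Conclusion.** The point holds as a mismatch between the declared design and the calculation. The arithmetic is right for independent subjects, but part 2 is not that design. The stated 80% is 77.7% with the named t-test before any clustering. With unit-level degrees of freedom it is about 73% to 76% if 16 units per arm contribute evenly (ICC 0.05 to 0.20), and lower with fewer units. The first figure rests on the article's inputs alone; the others rest on assumed ICCs, units per arm and equal unit sizes. A material shortfall caused by correlation itself is possible but not shown: it arises only if a small number of units supply most of the participants.

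**What to change.** Rewrite the sample-size paragraph for the cluster design. State:

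- the number of units per arm in part 2 and the expected completers per unit;
- an assumed ICC for the change in SCT, with a range, and the resulting design effect 1 + (m − 1) × ICC;
- that the test is two-sided, and that unit-level degrees of freedom are used;
- the power that 22 completers per group gives on those terms, in place of 80% (about 73% to 76% with 16 units per arm, lower with fewer).

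The cost is one paragraph and a less favourable power statement. No extra participants are needed if the sponsor accepts the lower figure. Keeping 80% would take more than 22 completers per group, by a number that can be fixed only once the units per arm and the ICC are stated.

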### Statistical methods

The statistical package, IBM/SPSS®, will be used to perform all data analyses. *P*-values less than 0.05 will be considered statistically significant. Descriptive statistics will be used to describe eating ability, oral health status, swallowing ability, quality of oral care, and swallowing-related QoL, among older individuals admitted to short-term care units. Descriptive statistics will also be used to describe the staffs’ perceptions of care quality. Univariate, bivariate, and multivariable regression (linear and logistic) analyses will be used to evaluate the associations between various dependent and independent variables. The Bonferroni correction will be used when multiple, pair-wise tests are performed on a single set of data, to reduce the chances of obtaining type I errors. Continuous variables will be presented as the mean value and standard deviation; categorical variables will be reported as the median and interquartile range. Differences between groups (e.g., intervention vs. control, older individuals vs. staff) will be assessed with independent sample t-tests (for continuous variables), chi-square tests (for categorical variables), and ANOVA or Kruskal-Wallis (for more than 2 groups).

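### Minor: the 22 per group matches a normal-approximation formula; with the t-test the protocol names, 22 completers per group give about 78% power, not 80%

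*Protocol article*

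**What the plan says.** The Sample size calculation section of the protocol article plans part 2 on the change in the Swallowing Capacity Test (SCT) and assumes normally distributed data. It sets the level first: "To retain an overall type I error of 5%, the type I error will be set to 2.5% for the primary endpoint". The spread comes from historical data: "we assume that the standard deviation of the change in SCT level will be 3 ml/s". The target is given as "To detect a critical difference of 2.8 ml/s in swallowing capacity between the intervention and control groups", with 80% power at the 2.5% level. The conclusion is that "a sample size of at least 22 subjects would be required to fulfill the study protocol in each group". The section then adds: "The total number of subjects included must be somewhat higher, to compensate for drop-outs". It gives no drop-out rate, and it does not name the formula or say whether the test is one-sided or two-sided.

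The Statistical methods section names the test for continuous variables: "Differences between groups (e.g., intervention vs. control, older individuals vs. staff) will be assessed with independent sample t-tests". The same section gives a general significance threshold of 0.05 for the project.

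**The concern.** The article states a power and names a test, and the two can be checked against each other without any outside figure. A sample size from the normal approximation treats the standard deviation as known. A t-test estimates it from the data and pays for that with a larger critical value. With large groups the difference disappears. With about 20 per group and a strict 2.5% level it is large enough to see.

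At stake is whether the article's power figure for part 2 holds for the test it describes. The 22 is also the base on which any later inflation would be built, whether for drop-out or for randomization by care unit. A base that is slightly too small carries its shortfall into those figures.

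**Working it through.** **Inputs.** From the Sample size calculation section: difference δ = 2.8 ml/s, standard deviation σ = 3 ml/s, type I error 2.5%, power 80%, and equal groups of n completers. From the Statistical methods section: independent-samples t-test. Assumed, because it is not stated: a two-sided test.

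**Step 1: reproduce the 22.** The normal-approximation formula is n = 2 (z₁₋α/₂ + z₁₋β)² (σ/δ)².

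With z₀.₉₈₇₅ = 2.2414 and z₀.₈₀ = 0.8416:

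n = 2 × (2.2414 + 0.8416)² × (3/2.8)² = 2 × 9.505 × 1.148 = 21.82, rounded up to 22.

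By the same approximation, power at n = 22 is 80.3%. The protocol's figure is therefore reproduced.

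**Step 2: check that other readings do not give 22.** Required n per group for 80% power:

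| Level | Normal formula | t-test |
|---|---|---|
| Two-sided 2.5% | 22 | 24 |
| One-sided 2.5% | 19 | 20 |
| Two-sided 5% | 19 | 20 |
| One-sided 5% | 15 | 15 |

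Of these, only the two-sided 2.5% normal formula returns 22. The formula and the sidedness are inferred from this match.

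**Step 3: power of the named test.** For a two-sample t-test, power comes from the noncentral t distribution with df = 2n − 2 and noncentrality λ = δ / (σ√(2/n)).

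At n = 22: df = 42, λ = 2.8 / (3 × √(2/22)) = 3.096, and the two-sided 2.5% critical value is 2.325 (against 2.241 for the normal).

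| n per group | df | λ | Critical t | Power |
|---|---|---|---|---|
| 22 | 42 | 3.096 | 2.325 | 77.7% |
| 23 | 44 | 3.165 | 2.321 | 79.7% |
| 24 | 46 | 3.233 | 2.317 | 81.7% |

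The smallest n reaching 80% is 24 per group, or 48 completers in total against 44. The shortfall at 22 is 80 − 77.7 = 2.3 percentage points.

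**Step 4: put the gap in proportion.** The standard deviation is given to one digit. With the same t-test at n = 22, power is 80.0% if the true standard deviation is 2.92 ml/s, and 74.7% if it is 3.1 ml/s. Over 2.5 to 3.5 ml/s, the range that rounds to 3, power runs from 91% down to 63%. The choice of formula matters far less than the uncertainty in this input.

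**The case against.** The strongest reply is that nothing was miscalculated. The 22 follows from a standard planning formula, the section names no other method, and the 2.3-point gap is small beside what rounding of the standard deviation alone can do (Step 4). This stands. It settles the weight of the point: a reader might infer an arithmetic error from the mismatch, but the documents show only an approximation that is slightly optimistic for the named test.

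A second reply is that the 77.7% rests on choices that the article leaves open. Sidedness is not stated, and at the general 0.05 threshold the t-test at 22 per group has 85.6% power. The t-test also appears in a generic list for the whole project, while the article elsewhere plans regression and says that age needs evaluating as a covariate for the SCT. This stands in part. The t-test sentence does not specify the primary SCT analysis by name, so the conclusion is about that test and no other. But the sentence gives intervention versus control as an example. The sample size section itself fixes 2.5% for the primary endpoint and derives its 22 from it, so the 80% has to be judged at that level.

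A third reply is that the 22 is a floor and that more participants will be included. This does not restore the 80%, because the extra participants are there to replace drop-outs. It does rule out a stronger reading: a reader might infer that the trial will stop at exactly 22 completers per group and so be underpowered. Nothing in the article makes 22 a stopping point, and no enrolment total for part 2 is fixed.

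Finally, part 2 is described as cluster randomized, so a power for independent participants is not the power of the trial under either formula. That is correct and is a separate matter. It is a reason to label the figure, and neither 22 nor 24 should be read as an allowance for clustering.

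**Conclusion.** The point holds and is minor. On the protocol's own inputs, the stated pairing of 22 completers per group with 80% power is right for the normal approximation. It is not right for the independent-samples t-test, which gives about 78% at 22 per group and reaches 80% only at 24. The conclusion assumes a two-sided 2.5% level, a standard deviation of 3 ml/s, a difference of 2.8 ml/s, equal groups and independent participants with complete data. The t-test figures are exact under those assumptions. The origin of the 22 is an inference, though a firm one. No effect on enrolment, analysis or interpretation of the trial has been shown.

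**What to change.** In the Sample size calculation section, keep 22 per group and restate the power as about 78%. Alternatively, give 24 as the minimum number of completers per group for 80% power. In either case:

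- state that the calculation is for a two-sided test at 2.5%;
- label the figure as assuming independent participants, before any allowance for drop-out or for cluster randomization.

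Restating the power changes one number and adds a short qualifying clause. It alters no enrolment total, and the stated power becomes slightly less favourable. Choosing 24 raises the minimum by 2 completers per group, 4 in total, so it is not as cheap as restating the power.

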### Statistical methods

The statistical package, IBM/SPSS®, will be used to perform all data analyses. *P*-values less than 0.05 will be considered statistically significant. Descriptive statistics will be used to describe eating ability, oral health status, swallowing ability, quality of oral care, and swallowing-related QoL, among older individuals admitted to short-term care units. Descriptive statistics will also be used to describe the staffs’ perceptions of care quality. Univariate, bivariate, and multivariable regression (linear and logistic) analyses will be used to evaluate the associations between various dependent and independent variables. The Bonferroni correction will be used when multiple, pair-wise tests are performed on a single set of data, to reduce the chances of obtaining type I errors. Continuous variables will be presented as the mean value and standard deviation; categorical variables will be reported as the median and interquartile range. Differences between groups (e.g., intervention vs. control, older individuals vs. staff) will be assessed with independent sample t-tests (for continuous variables), chi-square tests (for categorical variables), and ANOVA or Kruskal-Wallis (for more than 2 groups).

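### The significance threshold for the part 2 primary SCT endpoint is inconsistent: 2.5% in the sample size section, a general 5% in the analysis section, and a Bonferroni sentence that does not clearly reconcile them

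*Protocol article*

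**What the plan says.** The Protocol article, Sample size calculation, takes as the part 2 primary outcome variables (plural) the changes in SCT, "measured at the start and end of treatment, and at follow-up, 6 months later". The aim is stated as "To retain an overall type I error of 5" percent, and for this purpose "the type I error will be set to 2.5% for the primary endpoint". The sample size of at least 22 completers per group is computed at that level with 80% power.

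The Statistical methods section covers the whole project. Its only threshold is that P-values "less than 0.05 will be considered statistically significant". It names intervention versus control among the group comparisons it governs and does not repeat the 2.5% level. It has one multiplicity rule, aimed at false positive findings (quote cut short): "The Bonferroni correction will be used when multiple, pair-wise tests are performed on a single set of data, to reduce the chances of obtaining type". It does not say whether the two SCT time points fall under that rule.

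**The concern.** The two sections give different decision rules for the same comparison and do not refer to each other. An SCT p-value of, say, 0.03 fails the level in the sample size section and passes the general threshold in the analysis section. That is the verdict on the trial's main efficacy question. If the choice stays open until the data are seen, the more favourable rule can be picked afterwards.

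The Bonferroni sentence may or may not settle the matter. Its reference to pair-wise tests fits most naturally with comparisons among several groups, and the same section lists ANOVA and Kruskal-Wallis for more than two groups. Part 2 has two groups compared at two follow-up times. If those two comparisons were each judged at 0.05 with no correction, the stated overall 5% would be lost.

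**Working it through.** **Inputs from the protocol (Sample size calculation).** "To detect a critical difference of 2.8 ml/s in swallowing capacity between the intervention and control groups"; "the standard deviation of the change in SCT level will be 3 ml/s"; power 80%; type I error 2.5%; 22 per group. Sidedness is not stated; two-sided is assumed here and checked in step 1.

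**Step 1: which alpha does the sample size use?** For two means with equal groups, by normal approximation, n per group = 2 × (z for alpha + z for power)² × (SD/difference)².

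- (3/2.8)² = 1.148; z for 80% power = 0.842.
- Two-sided 0.025: z = 2.241; n = 2 × (2.241 + 0.842)² × 1.148 = 21.8, so 22. This is the plan's figure.
- Two-sided 0.05 (the same as one-sided 0.025): z = 1.960; n = 2 × (1.960 + 0.842)² × 1.148 = 18.02, so 19.
- One-sided 0.05: 15.

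With the noncentral t distribution, the first two become 24 and 20. Only two-sided 0.025 with the normal approximation gives 22 exactly, and 2.5% is also the level the text states. So 2.5% is the design level.

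**Step 2: overall error for two SCT comparisons.** The natural reading is two comparisons: change to end of treatment (t2) and change to 6 months (t3). Overall error = 1 − P(both |Z| ≤ c) for a bivariate normal pair, with c = 1.960 at 0.05 and c = 2.241 at 0.025. If independent, this is 1 − 0.95² = 0.0975 and 1 − 0.975² = 0.0494. The protocol gives no correlation between the two changes, so the values below are assumptions.

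| Assumed correlation | Each at 0.05 | Each at 0.025 |
|---|---|---|
| 0 | 9.75% | 4.94% |
| 0.5 | 9.07% | 4.65% |
| 0.7 | 8.35% | 4.30% |
| 0.9 | 7.04% | 3.62% |

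Whatever the correlation, the upper bounds are 0.05 + 0.05 = 10% and 0.025 + 0.025 = 5%. Both changes use the same participants and the same baseline SCT, so independence is implausible and the lower rows deserve more weight than the first.

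**Step 3: what the Bonferroni sentence would do.** If it covers exactly the two SCT comparisons, each is tested at 0.05/2 = 0.025. That is the level in the sample size section, and the overall error is at most 5%. If it covers only comparisons among several groups, it does not touch SCT and 0.05 remains. If it covers a wider set, the divisor is not two: with three tests the level would be 0.05/3 = 0.0167. Only the first reading makes the two sections agree.

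**The case against.** A reader might infer that the analysis section declares every p below 0.05 significant, and that the overall 5% is therefore not kept. The text does not support that, for three reasons.

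- The 0.05 rule is a general threshold for a project that also includes a descriptive part and staff questionnaires. The same section limits it with a Bonferroni rule.
- Bonferroni does not contradict a nominal 0.05. It works within it, by dividing the level or multiplying the p-value. For two comparisons it gives exactly the 2.5% that the sample size section sets.
- The sample size section speaks specifically about the part 2 primary endpoint and gives its reason. A specific statement can be taken to govern a general default.

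It can also be said that the two-comparison family is inferred. The section uses the plural for the outcome variables but the singular for the endpoint, and does not say where the other 2.5% goes. The correlations are assumptions too. Finally, this is a condensed article, and test-by-test levels are often left to an analysis plan.

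All of this limits the claim to a conditional one. It does not remove the inconsistency. The Bonferroni sentence is ambiguous on the very point at issue, nothing says that the 2.5% level overrides the general one, and the section giving the general threshold names intervention versus control. The point rests on two statements in the text that do not match, not on detail left out.

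**Conclusion.** The point holds as an inconsistent decision threshold for the part 2 primary SCT endpoint. The design level is 2.5%; the analysis section states 5% with no exception; the Bonferroni sentence would reconcile them on one reading but does not clearly do so. SCT p-values between 0.025 and 0.05 are affected.

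Inflation of the overall error to about 7–10% would follow only if both SCT comparisons were judged at an uncorrected 0.05. It rests on two comparisons being the family and on assumed correlations from 0 to 0.9. It is a risk left open by the wording, not an established breach of the stated 5%.

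**What to change.** State in Statistical methods that each of the two primary SCT comparisons between intervention and control (t2 and t3) is tested at two-sided 2.5%. Alternatively, state that the two are tested together by Bonferroni or Holm at an overall two-sided 5%. Add that 0.05 is the nominal level for the remaining analyses.

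Do not call all remaining analyses exploratory without further work. Table 1 also labels MEONF-II, ROAG and oral health status as primary outcomes, and all three are assessed in part 2. Such a label would need to be reconciled with Table 1 first.

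The cost is one sentence. The sample size does not change on this account, because it was already computed at 2.5%. An SCT p-value between 0.025 and 0.05 would no longer count as positive by itself. Under Holm it could still count if the other SCT comparison had passed 0.025.
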